#### Randomization

Each patient will be assigned a unique study code number, kept by the site Clinical PI and the clinical site study coordinators. Data relevant for randomization will be sent by email to the randomization manager at the Data Management and Monitoring Centre (DMMC) at Instituto de Salud Carlos III (ISCIII). The DMMC team generates the random sequence upon receiving the information from the clinical sites, i.e. patient code and category of the lesion. Participants are randomly assigned to either control or experimental group as per a computer-generated randomization schedule stratified by site using permuted blocks of random sizes (*n* = 4). Blocked randomization assures generation of study groups with the same size, and a close balance on the numbers in each group by site at any time during the trial. The random sequence is generated in an Excel spreadsheet via Random.org.

Data for randomization will be sent by text (SMS) where it is not possible to send by email. After computer-generated random allocation to either RC8 or RCA4, the randomization group will be provided by email to the site Clinical PI and the clinical site study coordinators. Randomization will be stratified by lesion categories I, II, or III, using a fixed block size within each strata. The target sample size is based on confirmation of *M. ulcerans* infection by polymerase chain reaction (PCR), which will be assessed after the randomization process.

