#### Efficacy analysis

Primary efficacy analysis will be determined for the PP PCR-positive population. The adjusted estimate of the difference (expressed as an absolute change and not a relative change) in the cure rate between the two arms will be presented along with 95% two-sided CI based on a stratified analysis using Cochran-Mantel–Haenszel (CMH) weights. For the statistical analysis, BU categories I-III will be the three strata. The difference in cure rate between the two treatment groups (RC8 *vs.* RCA4) and the corresponding 95% CI will be calculated. Treatment with RCA4 will be declared non-inferior to treatment with RC8 if the lower bound of a two-sided 95% confidence interval (CI) for the difference in cure rates (expressed as an absolute change and not a relative change) between the two treatment arms is greater than − 10%. A superiority hypothesis will be tested once non-inferiority is proven. Superiority can be concluded if the lower bound of a two-sided 95% confidence interval for the difference in cure rates (expressed as an absolute change and not a relative change) between the two treatment arms is greater than 0%. Details for analysis of secondary efficacy outcomes will be included in the Statistical Analysis Plan (SAP).

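### The Randomization section describes two schemes that cannot both be true; if blocks are fixed at 4 and staff know earlier allocations in the stratum, about a third of allocations are certain in advance

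*Protocol article*

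**What the plan says.** All in the protocol article.

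- **Randomization, first description.** Patients are assigned "as per a computer-generated randomization schedule stratified by site using permuted blocks of random sizes". A single size, 4, follows in brackets. The text claims "a close balance on the numbers in each group by site at any time during the trial".
- **Randomization, second description.** "Randomization will be stratified by lesion categories I, II, or III, using a fixed block size within each strata".
- **Randomization, timing and inputs.** "The DMMC team generates the random sequence upon receiving the information from the clinical sites"; the information listed is patient code and lesion category.
- **Abstract (Methods).** Participants are stratified by lesion category; site is not mentioned.
- **Efficacy analysis.** For the Cochran-Mantel-Haenszel (CMH) estimate, "BU categories I-III will be the three strata".
- **Study design; Study setting.** The trial is open-label, at three sites.
- **Who knows what.** Each allocation is emailed to the site Clinical PI and the site study coordinators (Randomization). Clinical investigators at each site score the lesion by consensus, and a site clinician or delegate assesses eligibility (Screening and informed consent).

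**The concern.** A reader cannot tell how patients are allocated. Two features conflict: block type (random or fixed) and stratification factor (site or lesion category).

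This matters for concealment. In an open-label trial, site staff learn each allocation as it is made. If blocks are short and of fixed, known size, they can sometimes work out the next one. Central allocation hides the list but does not prevent this inference. Someone who can foresee the arm can influence who is enrolled, when, and under which category. Few failures are expected, so a small imbalance in prognosis could affect a non-inferiority conclusion.

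**Working it through.** **1. The two descriptions side by side**

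| Feature | First description | Second description | Elsewhere |
|---|---|---|---|
| Stratum | Site | Lesion category I–III | Category only (abstract, primary analysis); category and patient code are the listed inputs |
| Block size | Random, but only 4 given | Fixed | – |

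The block-size row has no consistent reading. The stratum row has one, site by category, but the text does not state it.

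**2. The plan's own figures**

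The article gives no predictability figure, so I checked the sample size that sets the scale. Inputs (Sample size section): cure 95.9% in both arms, margin 10 points, one-sided alpha 2.5%.

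n = (1.960 + 0.842)² × 2 × 0.959 × 0.041 / 0.10² = 61.7, so 62 per arm. Then 62/0.95 = 65.3, so 66; and 66/0.95 = 69.5, so 70. All three match.

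Expected failures are 62 × 0.041 = 2.5 per arm, about 5 in total.

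**3. Fixed blocks of 4, 1:1, earlier allocations in the stratum known**

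- Certain in advance: the 4th always; the 3rd when the first two agree (probability 1/3). (1 + 1/3)/4 = **33.3%**.
- Best guess right: positions 1 to 4 give 1/2, 2/3, 2/3 and 1. The sum is 2.83, and 2.83/4 = **70.8%**, against 50% by chance.

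In a simulation of 140 patients with incomplete last blocks, the certain share is 32% for site strata, 31% for site by category, and 32% for category strata when staff know every site's allocations.

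**4. Category strata shared by three sites, staff seeing only their own**

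Let q be a site's share of patients. The 3rd allocation is certain with probability q²/3 (both earlier patients at this site and in the same arm). The 4th is certain with probability q² (both patients of the completed arm at this site). The average over four positions is q²/3. Weighting by q over sites gives Σq³/3.

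- Equal sites: 3 × (1/3)³/3 = 3.7% (simulated 3.5%).
- Shares of 60/20/20, an assumption: (0.216 + 0.008 + 0.008)/3 = 7.7% (simulated 7.6%).

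Both grant staff knowledge of where each block starts, which they would not normally have, so **about 4–8%** is on the high side.

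**5. What varying sizes would achieve**

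- Certain predictions: with sizes 4 and 6 equally likely, the imbalance reaches its maximum of 3 only when a block of 6 opens with three alike (probability 2/20). Allocations that follow this state: (1/2 × 1/10)/5 = 1%, or 3% counting the rest of that block. For sizes 2, 4 and 6: (1/3 × 1/10)/4 = 0.8%, or 2.5%. Staff who also learnt the set of sizes could be certain somewhat more often, hence the need to withhold it.
- Best guess: backing the arm that is behind needs no knowledge of block size. For sizes 2, 4 and 6, (1.50 + 2.83 + 4.10)/12 = 70.3%, barely below 70.8%.

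**6. Sensitivity of the conclusion**

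Unstratified Wald 95% lower bounds, 62 per arm, failures on RC8 versus RCA4:

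| Failures | Lower bound |
|---|---|
| 3 v 3 | −7.6% |
| 3 v 4 | −9.7% |
| 3 v 5 | −11.9% |
| 2 v 3 | −8.5% |
| 2 v 4 | −10.8% |

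From 3 v 3, two extra RCA4 failures cross the margin; from 2 v 3, one does.

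**The case against.** The case for treating this as a wording slip has several parts.

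- **The strata are compatible.** Neither sentence says only, so site by category is a fair reading. This stands as a possibility. It does not settle the block-type conflict, and it is the reading under which the one-third figure applies.
- **The one-third figure is conditional.** A reader might infer that a third of this trial's allocations are predictable. The article does not support that: it requires blocks truly fixed at 4 and staff who know the earlier allocations in the stratum. Under category strata shared across sites it can be 4–8%. This stands.
- **Selection has limits.** Diagnosis uses WHO scoring by consensus, lesions are measured and photographed, and the primary population is PCR-positive. This narrows the scope for discretionary enrolment but leaves timing and category assignment open. No selection has been shown, and a selected patient is not a certain failure.
- **The list may already be locked.** A reader might infer from "The DMMC team generates the random sequence upon receiving the information from the clinical sites" that no list exists beforehand. The same section refers to a schedule, so the phrase may only mean that an allocation is issued then. The article leaves this unclear.
- **Site need not enter the analysis.** A reader might infer that omitting site from the CMH strata is an error. That would follow only if site is a randomisation factor, and no bias from omission is shown. With about 5 failures, at least four of nine site-by-category strata would have none.
- **Disclosure cannot be undone.** The article is published, so deleting the block size does not make it secret. This stands; only different sizes for remaining patients help.

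**Conclusion.** The contradiction is real and sits within one section. The block-type conflict cannot be reconciled; the stratum conflict can be, but only by a reading that the text never states.

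The consequence for concealment is conditional. About 33% of allocations are certain in advance if blocks are fixed at 4 and staff know the earlier allocations in their site or site-by-category stratum. About 4–8% are certain if category strata span the three sites and staff see only their own (equal shares, or an assumed 60/20/20). The share is lower still if sizes vary and are withheld. Which case applies depends on the very points the article leaves contradictory.

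This is a defect of specification that may weaken concealment, not evidence that allocation was subverted. It is worth correcting because site staff receive each allocation and judge eligibility, and because one or two extra failures can move the result across the margin.

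**What to change.** 1. State one set of strata, category or site by category, and make the Randomization section, abstract and balance claim agree with it.
2. State one block type. For any patients still to be randomised, use randomly varying block sizes, held at the data centre and not disclosed to sites. Remove both the fixed-block wording and the bracketed size of 4.
3. Report the scheme actually used for patients already randomised. Recruitment began in December 2021 and was planned to November 2023 (Trial status).
4. Say whether the schedule exists before a patient's data arrive.
5. Keep the category-stratified CMH analysis; adding site is optional.

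The change should not be presented as making allocation unguessable. It removes nearly all certain predictions, while best-guess accuracy stays near 70% with sizes 2, 4 and 6.

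The cost is protocol wording and a new list for remaining patients, with no extra patients or visits.

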#### Type of data collected

The data to be collected from study participants will include stage and presentation of the disease, i.e. ulcer, non-ulcer; lesion size and category; digital photograph of the lesion, study site; and demographic data. The BU01.N form will be completed according to the WHO recommendations [24]. All data will be recorded in the Case Report Form (CRF) for every patient.

#### Data sharing and access

We will generate a metadata record describing all datasets arising from the project and make this available through an appropriate repository (e.g. DRYAD https://datadryad.org/). This will act as a site for long-term curation and preservation. Scientific reports will be written and submitted to peer-reviewed journals during and at the end of the project. Data underpinning these articles will be made available for access.

#### Microbiological analysis

Diagnostic procedures will depend on the presentation of the disease. In non-ulcerated lesions, fine-needle aspiration (FNA) will be the usual sampling procedure with two samples taken per lesion. In ulcerated lesions, two cotton wool swabs from undermined ulcer edges will be taken.

All sample collection procedures will follow WHO guidelines [29]. For the purpose of this clinical study, all specimens will be examined for *M. ulcerans* confirmation by PCR using insertion sequence IS*2404* and direct microscopy for acid-fast bacilli (AFB) [30]. In addition, microbiology cultures and drug susceptibility testing, including the assessment of synergistic drug interactions in clinical isolates, will also be performed as part of this trial at baseline and in the case of relapse of unhealed lesions to test for possible development of resistance or loss of synergy.

#### Treatment

Two treatment regimens will be used in this clinical study protocol (Table 2):WHO-recommended standard (control): 8 weeks of rifampicin plus clarithromycin [8].Investigational: 4 weeks of rifampicin plus clarithromycin plus amoxicillin/clavulanate.

**Table 2 Tab2:** Clinical trial treatment cohort regimens

Treatment cohort	Dose	Posology	Treatment length
Standard arm: [RC8]	^**1**^Rifampicin 600 mg	Daily	8 weeks
	^**1**^Clarithromycin 500 mg	Twice daily	8 weeks
Investigational arm: [RCA4]	^**1**^Rifampicin 600 mg	Daily	4 weeks
	^**1**^Clarithromycin 500 mg	Twice daily	4 weeks
	^**2**^Amoxicillin/clavulanate 1000/125 mg	Twice daily	4 weeks

^1^Dose indicated are for a 60 kg adult and will be standardized according to patient body weight following the WHO guidelines [31]. Rifampicin (R), 10 mg/kg; Clarithromycin (C) 7.5 mg/kg

^2^Dose of amoxicillin/clavulanate (A) 1000/125 mg twice daily, which makes a total of 2000/250 mg/day, for patients over 40 kg, and 22.5/5.6 mg/kg twice daily, which makes a total of 45/11.25 mg/kg/day, for those equal and below 40 kg. For children, posology will be adapted to the age of the patient according to drug manufacturer indications. There are no current recommendations for the use of amoxicillin/clavulanate for BU infections. Those indicated above are recommended doses for complicated infections according to manufacturer indications

During the trial period of antibiotic treatment, patients will be either admitted to the hospital, or receive directly observed therapy at one of the participating satellite health centres. All RC8 or RCA4 treatment will be fully supervised by health care staff to avoid possible side effects (Table 3).

**Table 3 Tab3:** List of possible effects due to rifampicin, clarithromycin, and amoxicillin/clavulanate

	**Rifampicin**	**Clarithromycin**	**Amoxicillin/clavulanate**
More common	None	None	Nausea, vomiting, headache, diarrhoea, gas, stomach pain, skin rash or itching, white patches in your mouth or throat
Less common/rare	Chills, difficult breathing, dizziness, fever, headache, itching, muscle and bone pain, shivering, skin rash and redness; bloody or cloudy urine, increased frequency of urination or amount of urine, loss of appetite, nausea or vomiting, sore throat, unusual bleeding or bruising, unusual tiredness or weakness, yellow eyes or skin	Loss of appetite, nausea, dyspepsia; changes in taste and smell sensation; headache; ringing or buzzing in the ears (tinnitus), dizziness; liver enzyme elevation; allergic skin reactions including Stevens-Johnson syndrome; blood dyscrasias; reversible loss of hearing	Watery or bloody diarrhoea; pale or yellowed skin, dark coloured urine, crystalluria, fever, confusion or weakness; easy bruising or bleeding; skin rash, bruising, severe tingling, numbness, pain, muscle weakness; agitation, confusion, unusual thoughts or behaviour, seizures (convulsions); nausea, upper stomach pain, itching, loss of appetite, clay-coloured stools, jaundice (yellowing of the skin or eyes), or severe skin reaction; sore throat, swelling in face or tongue, burning in eyes, skin pain, followed by a red or purple skin rash that spreads (especially in the face or upper body) and causes blistering and peeling

Adverse events will be registered and coded for further reporting following MedDRA guidelines.

#### Follow-up

Follow-up will be according to the visit schedule (Fig. 2) and will take place at the clinical sites, outpatients clinic, and/or in the communities. Patients missing clinic appointments will be followed up in the community by the study team. This information and the reasons for non-attendance will be noted in the patient’s file in order to implement strategies and measures to prevent future loss to follow-up.

For visits outside the scheduled ones, visits that are early in the follow-up line (visits scheduled up to week 14), a ± 7 days window can be accepted, and a ± 14 days window for follow-up visits which are late in the follow-up line (visits at 6 and 12 months), without a protocol deviation being reported. In both scenarios, the days are counted from the day (before or after, depending on the case) for which the visit was scheduled. If the time of the visit is outside this protocol window, data can still be collected; however, a protocol deviation should be reported.

Patients will always be followed up by local clinicians (in a non-blinded manner) as they usually do in normal BU care. Patients will have clinical assessment of the lesions and scars at every visit or any time the patient self-reports (any reason), or a paradoxical reaction is suspected/diagnosed. Local clinicians will take any decisions regarding wound debridement and skin grafting, according to standard care procedures. Any decision for excision surgery will be delayed to 14 weeks after initiation of antibiotic treatment according to recent findings showing that BU patients benefited from delaying the decision to operate from 8 to 14 weeks [32]. In addition, a clinical expert panel (Technical Expert Panel, TEP), blinded to treatment allocation in order to make objectives comparisons, will assess the need of excision surgery in both treatment arms. Their assessment will be conferred with that of the local clinicians.

#### Study schedule

Study set up will last 12 months, whereas recruitment is estimated to last 24 months. Hence, last patient, last visit (LPLV) will occur 36 months after the first patient is randomized. Study close out will be 6 months after LPLV.

#### Discontinuation from the study medication

Patients who meet study eligibility criteria, give informed consent (or assent plus consent by caretakers) but who may not have completed the full treatment course of antibiotic therapy will be discontinued from the study medication for any one of the following reasons:Observation of rapid enlargement of the lesion despite drug treatment, and not attributed to a paradoxical response.Presence of SAE or adverse drug reaction of NIH/NCI Common Toxicity Criteria [33] grade 3 or 4 that prevent adherence to treatment.Need to use any drug with anti-mycobacterial activity or likely to interfere with interpretation of the results during the treatment period.Allergic reaction to a study drug.Observation of any new condition or situation (including pregnancy, major trauma, or severe immune compromise) developing during the trial, which in the judgement of the investigation team, may interfere with continued participation in the study.At the request of the subject / withdrawal of consent or assent.Non-compliance with scheduled follow-up visits.Non-compliance with medication.If the investigator considers that a patient’s health will be compromised due to AEs, SAEs, or a concomitant illness that develops after entering the study.

They will however be followed up for safety and included in the analysis.

#### Procedures for withdrawal from the study

Subjects withdrawn from the study will not be replaced (5% drop out has been assumed for power calculations) but will be included in the analysis. Subjects who withdraw will be invited to continue attending study clinics for routine care and measurements and will be offered the standard of care according to the PNLLUB guidelines. Reasons for withdrawal will be recorded in the CRF and in the subjects’ medical notes and will be taken into account to prevent any potential loss of patients.

### Pharmacovigilance

Safety of the two treatment regimens will be assessed through routine monitoring of AEs. At each of the scheduled follow-up visits, patients will be enquired about current AEs or any events observed during the period prior to the visit. In addition, evaluation of haematology and blood chemistry parameters, performing ECG, regular measurement of vital signs, and physical examinations will be made at scheduled follow-up according to the visit schedule. AEs could also be detected when reported by the patient during or between visits. At randomization, patients will be given two telephone numbers, which they can call or send a text message/WhatsApp in the event of experiencing an AE. All AEs causing discontinuation, interruption, or adjustment of the trial therapy must be recorded in the AE section of the CRF, regardless of the assumption of a causal relationship. Documentation of AEs includes date of onset and offset, pattern, duration, intensity, impact, actions taken, severity, and outcome.

The Clinical PI should also evaluate the probability of a causal relationship of the AE to the trial medication. Any patient who develops an AE will be followed up and treated appropriately until he/she returns to normal condition. Any treatment, if necessary, will be recorded in the CRF.

All AEs (including laboratory abnormalities) will be recorded in the CRFs. After the trial has been completed or terminated, all recorded AEs will be listed, evaluated, and discussed in the final report.

Furthermore, in order to ensure the safety of the patient, from the moment that informed consent has been obtained from the patient and until 30 days after the patient has discontinued from the study drugs, any AE must be reported immediately to the site study coordinator and the site PI and to the Data Safety and Monitoring Board (DSMB) within 24 h of patient’s notification or identification of the occurrence by the clinical staff, regardless of suspected causality.

Any SAE must be reported to the DSMB, the Benin Ethics Committee (EC), and the Sponsor within 24 h of patient’s notification or identification of the occurrence by the clinical staff, regardless of suspected causality.

### Endpoints of the study

#### Definitions of the populations for analysis

Intention-to-Treat Exposed (ITT-E): this population will consist of all randomized patients who receive at least one dose of randomized study medication. Patients will be assessed according to their randomized treatment, regardless of the treatment they receive.Per Protocol (PP): this population will consist of subjects in the ITT-E population who complete the study and are not major protocol violators.Per Protocol (PP) PCR-positive population: The PP PCR-positive population includes those randomized patients with a clinical diagnosis of very likely BU or likely BU, PCR-positive, and with no major violations of the protocol. Unless stated otherwise, the PP PCR-positive population will be used for efficacy analyses.Intention-to-Treat Exposed (ITT-E) PCR-positive population: The ITT-E PCR-positive population includes those randomized patients with a clinical diagnosis of very likely BU or likely BU, PCR-positive that have, at least, taken one dose of the study drugs. This population might include major violators of the protocol. The ITT-E PCR-positive population will be also used for secondary analysis of efficacy.Per Protocol (PP) Clinical Diagnosed (CD) population: The PP CD population includes those randomized patients with a clinical diagnosis of very likely BU or likely BU and with no major violations of the protocol. This population includes both PCR-positive and PCR-negative. The PP CD population will be also used for secondary analysis of efficacy.Intention-to-Treat Exposed (ITT-E) Clinical Diagnose (CD) population: The ITT-E CD population includes those randomized patients with a clinical diagnosis of very likely BU or likely BU that have, at least, taken one dose of the study drugs. This population might include both PCR-positive and PCR-negative and major violators of the protocol. The ITT-E CD population will be also used for secondary analysis of efficacy.Safety: The Safety Population (SP) is defined as all subjects who receive at least one dose of randomized study medication. Subjects will be analysed according to the actual treatments received. Unless otherwise stated, the SP will be used for safety analyses.Pharmacokinetic (PK): the PK population is defined as the participants in the SP who receive at least one dose of randomized study medication and have at least one evaluable PK sample. Participants will be analysed according to the treatment actually received.

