### Methods/design

#### Study design

BLMs4BU study is a Phase II, randomized, controlled, open-label, parallel-group, non-inferiority, multi­centre trial, with two treatment arms:Standard [RC8]: RIF plus CLA (RC) therapy for 8 weeks; andInvestigational [RCA4]: standard (RC) plus AMX/CLV (A) for 4 weeks.

The flow chart of the clinical trial study design and timelines are depicted in Figs. 1 and 2. In addition, a PK and microbiology study will be also performed in a complementary manner. Details of ethics approval are provided at the end of the manuscript.

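### All three intention-to-treat sets drop randomised patients who take no dose, in an open-label trial where the site knows the arm before dosing, so no analysis set keeps everyone randomised

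*Protocol article*

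**What the plan says.** Under Definitions of the populations for analysis, the protocol article describes the ITT-E set thus: "this population will consist of all randomized patients who receive at least one dose of randomized study medication". The ITT-E PCR-positive and ITT-E CD sets are limited to patients "that have, at least, taken one dose of the study drugs". ITT-E patients are analysed in the arm to which they were randomised. The per-protocol sets remove major violators, and the safety and PK sets also need a dose. No set of all randomised patients is defined.

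Study design describes the trial as "Phase II, randomized, controlled, open-label, parallel-group, non-inferiority". Under Randomization, after allocation, "the randomization group will be provided by email to the site Clinical PI and the clinical site study coordinators". Follow-up says that local clinicians are not blinded.

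On the use of the sets, Efficacy analysis states: "Primary efficacy analysis will be determined for the PP PCR-positive population". The population definitions add: "The ITT-E PCR-positive population will be also used for secondary analysis of efficacy". The same secondary role is given to ITT-E CD.

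Procedures for withdrawal from the study says that withdrawn subjects are not replaced "but will be included in the analysis". It does not name the population.

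**The concern.** Leaving out never-dosed patients does little harm when the decision not to start cannot depend on the arm, as under blinding. Here the arms differ visibly (four weeks of three study treatments against eight weeks of two), and the site must know the arm to give the first allocated dose. A refusal or withdrawal between allocation and first dose can therefore be related to the arm, and the ITT-E definitions would remove it.

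The primary analysis is per protocol and so already excludes patients after randomisation. The ITT-E analyses are the counterweight. If they too exclude patients after the arm is known, no analysis fully preserves the randomisation. Secondary endpoints also places the discontinuation and compliance rates in the ITT-E and per-protocol sets, so a patient who rejected the allocated arm before dosing would be missing from the ITT-E rates meant to show it.

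There is also a mismatch of text. A patient who withdraws before any dose is to be included in the analysis according to the withdrawal section, but belongs to none of the ITT-E sets.

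**Working it through.** **The plan's own figures (Sample size).** Inputs: cure rate 95.9% in both arms, margin 10 points, one-sided alpha 2.5%, power 80%.

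- n per arm = (1.960 + 0.842)² × 2 × 0.959 × 0.041 / 0.10² = 61.7, rounded up to 62, as stated.
- 62 / 0.95 = 65.3, rounded up to 66 PCR-confirmed patients, as stated.
- 66 / 0.95 = 69.5, rounded up to 70 clinically diagnosed patients, as stated.

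The point changes none of these.

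**Scale.** Expected failures per arm are 66 × 0.041 = 2.7, so 3 is used below. One patient in 66 is 1.5 points of cure rate.

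**Illustration.** Assumptions: 66 PCR-positive patients randomised per arm; RC8 63/66 cured (95.45%); 3 failures among dosed RCA4 patients; k never-dosed patients, all in RCA4. The protocol gives no value for k. All RC8 patients are taken as dosed, and no outcomes are missing.

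Lower bound = d − 1.96 × √[p₁(1−p₁)/n₁ + p₀(1−p₀)/n₀], where d = p₁ − p₀, 1 is RCA4 and 0 is RC8.

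| k | Handling | RCA4 cured | d (points) | SE (points) | Lower bound |
|---|---|---|---|---|---|
| 0 | – | 63/66 | 0.00 | 3.63 | −7.1 |
| 1 | excluded | 62/65 | −0.07 | 3.65 | −7.2 |
| 1 | kept as not cured | 62/66 | −1.52 | 3.90 | −9.2 |
| 2 | excluded | 61/64 | −0.14 | 3.68 | −7.4 |
| 2 | kept as not cured | 61/66 | −3.03 | 4.15 | −11.2 |

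With k = 1 both handlings stay inside −10. With k = 2 the ITT-E result would meet the margin and the all-randomised result would miss it.

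**If the undosed are balanced.** With one never-dosed patient in each arm, both kept as not cured (62/66 in each), d = 0 and the bound is −8.1. With two in each arm (61/66 in each) it is −9.0. Neither crosses the margin, so the effect comes from imbalance.

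**Dependence on the interval.** The planned interval is stratified with CMH weights and cannot be computed without data by lesion category. A Newcombe score interval, unstratified, gives −8.7 (excluded) and −10.5 (kept as not cured) at k = 1, and −8.9 and −12.5 at k = 2. The number of patients needed to cross the margin is therefore specific to the method.

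**The case against.** The choice is disclosed: the sets are named as exposed sets and the condition is written out. Every deviation after the first dose stays in the allocated arm, and ITT-E PCR-positive and ITT-E CD may include major violators. If nobody goes undosed, ITT-E is the all-randomised set. Consent comes before enrolment, and treatment is given in hospital or directly observed, so few such patients are likely. The ITT-E sets are secondary and the primary result does not rest on them. All of this stands, and it is why the point is minor.

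Three stronger readings are not supported.

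- *One omitted patient decides the trial.* A reader might take 62 per arm with 3 failures against 4, where the Wald bound is −9.7, and note that a fifth failure gives −11.9. But 62 is the evaluable number after loss to follow-up, not the 66 relevant to intention to treat, and the starting point is already at the margin. At the planned cure rate with 66 per arm, one patient leaves the Wald bound at −9.2. The Newcombe result shows that this is close, but either way the patient must be in RCA4 and counted as a failure, and the protocol sets no such rule.
- *The withdrawal section contradicts the population definitions.* It names no population, and a patient who withdraws after a dose satisfies both. They clash only for withdrawal before any dose.
- *Exclusions will depend on the arm.* The text shows only that they can. The named recipients of the allocation are site staff; that the patient also knows before dosing is a fair inference from the open-label design, not a statement in the protocol.

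The multiple imputation under Analysis of missing outcome data does not answer the point. It concerns missing outcomes and is not said to bring never-dosed patients back.

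**Conclusion.** The point holds as a minor weakness of definition. All three ITT-E sets condition on something that happens after an open allocation, no set keeps all randomised patients, and the withdrawal section does not fit these definitions for anyone who leaves before dosing.

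The likely size is small, with 0 to 2 never-dosed patients per arm as an assumption. In the Wald illustration the non-inferiority conclusion of this secondary analysis changes only from two such patients, all in RCA4 and all counted as not cured. That rests on 66 per arm, 3 failures among dosed patients in each arm, and an unstratified interval. Counting every undosed patient as not cured is the unfavourable extreme. The primary analysis and the sample size are unaffected.

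**What to change.** 1. Define the ITT PCR-positive and ITT CD sets as all randomised patients (PCR-positive, or clinically diagnosed as very likely or likely) analysed as allocated, whether or not a dose was taken.
2. For never-dosed patients, time the 12-month outcome from randomisation, because Primary endpoint counts from treatment initiation and they have none.
3. Use the observed outcome where there is one. Otherwise use the multiple imputation already planned, with a sensitivity analysis that counts them as not cured.
4. Report the number of never-dosed patients and their reasons by arm.
5. Name the population meant in Procedures for withdrawal from the study, so that it agrees with the definitions.
6. Keep the one-dose condition for the safety and PK sets only.

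The cost is a few sentences, slightly more analysis work, and a second time origin for any undosed patients. Sample size, recruitment and treatment do not change. If nobody goes undosed, the results are the same as under the present definitions.
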